## Abstract

**Background:**

Physicians´ lack of knowledge contributes to underuse of insulin and poor glycemic control in adults with diabetes mellitus (DM). Traditional continuing medical education have limited efficacy, and new approaches are required.

**Objective:**

We report the design of a trial to assess the educational efficacy of InsuOnline, a game for education of primary care physicians (PCPs). The goal of InsuOnline was to improve appropriate initiation and adjustment of insulin for the treatment of DM. InsuOnline was designed to be educationally adequate, self-motivating, and attractive.

**Methods:**

A multidisciplinary team of endocrinologists, experts in medical education, and programmers, was assembled for the design and development of InsuOnline. Currently, we are conducting usability and playability tests, with PCPs and medical students playing the game on a desktop computer. Adjustments will be made based on these results. An unblinded randomized controlled trial with PCPs who work in the city of Londrina, Brazil, will be conducted to assess the educational validity of InsuOnline on the Web. In this trial, 64 PCPs will play InsuOnline, and 64 PCPs will undergo traditional instructional activities (lecture and group discussion). Knowledge on how to initiate and adjust insulin will be assessed by a Web-based multiple choice questionnaire, and attitudes regarding diabetes/insulin will be assessed by Diabetes Attitude Scale 3 at 3 time points—before, immediately after, and 6 months after the intervention. Subjects´ general impressions on the interventions will be assessed by a questionnaire. Software logs will be reviewed.

**Results:**

To our knowledge, this is the first research with the aim of assessing the educational efficacy of a computer game for teaching PCPs about insulin therapy in DM. We describe the development criteria used for creating InsuOnline. Evaluation of the game using a randomized controlled trial design will be done in future studies.

**Conclusions:**

We demonstrated that the design and development of a game for PCPs education on insulin is possible with a multidisciplinary team. InsuOnline can be an attractive option for large-scale continuous medical education to help improving PCPs´ knowledge on insulin therapy and potentially improving DM patients´ care.

**Trial Registration:**

Clinicaltrials.gov: NCT01759953; http://clinicaltrials.gov/show/NCT01759953 (Archived by WebCite at http://www.webcitation.org/6Dq8Vc7a6).

## Introduction

Achieving and maintaining good glycemic control is the mainstay of treatment of diabetes mellitus (DM) [1]. Unfortunately, only 24-56% of patients with DM are within the goal of the glycated hemoglobin A1c <7%, in most countries [2,3].

Worldwide, according with public health trends, most diabetics are treated by primary care physicians (PCPs) [4], but these professionals lack knowledge and confidence on several aspects of DM management [5], specially regarding insulin use [6]. This contributes to the common problem known as clinical inertia, "the failure to advance therapy when indicated" [7], underuse of insulin [8], and poor glycemic control.

Continuing medical education (CME) on DM and insulin is often advocated as a solution to optimize the knowledge and the practice of PCPs [9]; however, traditional CME activities (such as lectures and group discussions) have small and short-lasting efficacy [10]. Thus, new educational methods are urgently required.

Digital games are currently one of the six greatest trends in higher education [11], since they are able to "create a tight marriage among content, game play, and valued ways of thinking and acting" [12]. One of the reasons for increasing interest in games for higher and professional education is the huge familiarity of most college students with the medium [13]. Most medical students, for instance, even those who do not play video games, have highly favorable views about the use of video games and new technologies in medical education [14]. However, the most compelling reason for adopting learning games, probably, is their pedagogical adequacy. Good learning games are usually built by the same rules that guide the design of effective learning activities, which include stimulus to players´ intrinsic motivation, practice and repetition, effective feedback, arousal of positive feelings, intensity of the experience, and learner choice/involvement [15]. In the medical area particularly, the use of games and simulators for learning clinical skills has the additional advantage of increasing the safety of real patients [16].

In the field of diabetes, some games for education of patients [17-19], and a few technology-based initiatives for education of health professionals [10,19-25] have been described, but to our knowledge, no game have been reported for education of health professionals on diabetes or insulin.

In this paper, we report the design and development of a serious personal computer game for teaching PCPs about initiation and adjustment of insulin in the treatment of DM, and describe the design of a randomized controlled trial to assess if the game can be educationally effective.

## Methods

### Game Design

A multidisciplinary team was assembled, consisting of clinical endocrinologists ([name], [name]), experts in medical education ([name], [name], [name]) and software developers/game designers ([name], [name]). The endocrinologists compiled a list of main topics on insulin initiation and adjustment for treatment of adults with DM, in the context of a primary health care setting, outlining the minimum curriculum of the game (Textbox 1).

Periodic team meetings were scheduled during the design and development phases, to review each step, correct problems, and make decisions for the following stages, in an iterative process. The group agreed that the game should be developed in a way to satisfy 2 basic conditions: (1) to be educationally adequate, and (2) to be self-motivating and attractive to the final users.

The minimum curriculum describing teaching topics on insulin therapy selected for inclusion in the game.1. Goals of glycemic control in adults with DM2. When to start insulin in type 2 DM3. How to start insulin in type 2 DM (bedtime scheme)4. Recommendations on insulin use (storing, injection technique, and devices)5. Hypoglycemia: prevention, recognition, and treatment6. Self-monitoring of blood glucose7. Types of insulin: when to use which (NPH, regular)8. Oral antidiabetic drugs associated with insulin9. How to adjust insulin dosage10. How to intensify insulin therapy in type 2 DM (basal-plus scheme)11. How to start insulin in recent-onset severe type 2 DM (basal-bolus scheme)12. Type 1 DM: how to recognize it and how to start treatment13. How to recognize and manage diabetic ketoacidosis

### Storyline

The authors ([name], [name]) developed the story of InsuOnline based on Joseph Campbell´s classical description of the myth cycle [26]. The story begins in a primary health care clinic, where an experienced medical doctor (the mentor) wants to go on vacation, but he cannot leave without getting a substitute physician to take care of his diabetic patients. So, he randomly chooses a younger doctor to replace him (ie, the player´s avatar). The player proceeds to see a series of diabetic patients who usually require insulin initiation or adjustment in order to obtain a better glycemic control. If the player successfully reaches the end of the game, the mentor character is finally able to go on vacation, and the player´s character is thanked by the mentor, obtains the respect of the nurse and the patients, and a brand new office. The main objective of the game is to have each player correctly initiate or adjust insulin for each patient case.

### Level Design

We created 16 diabetic patients, reflecting common clinical scenarios in actual primary health care clinical practice, each one corresponding to at least one of the topics of game´s minimum curriculum. Each game level has a new patient presented to the player. The patients/levels are disposed in order of increasing complexity. The player´s avatar must make decisions on the best therapeutic option to improve each patient´s glycemic control at every level. Right decisions lead to progression to the next level, and incorrect choices lead to a new attempt at the same level. The basic structure of each level is shown in Figure 1.

**Figure 1 figure1:**
[figure not shown]
Basic structure of an InsuOnline level.

### Interactive Components and Game Elements

Several ways of interaction and game elements were included to create a pleasant experience and to maximize players´ intrinsic motivation. The player can read patients´ clinical charts, dialogue with them (be choosing among a few options of "talks"), see their lab tests and fingertip glucose readings, review their physical exam, answer quiz challenges, solve puzzles, get tips from the mentor and a nurse, and, prescribe insulin. Sound track, score, visual and sound effects, patients' mood (the patient gets angry if the player makes too many errors), and between-levels animation scenes (machinimas) were also included, to improve the gaming experience and players´ motivation.

### Pedagogical Elements

Several pedagogical elements were included in the game, aiming for the best educational effects. These were based on the principles of adult learning and problem-based learning, including motivation, goal-orientation, relevancy-orientation, self-pacing, timely and appropriate feedback, reinforcement of learning, informal environment, contextualization, and practical (ie, hands-on) approach with active participation of the learner [27,28].

The game gives immediate feedback (presented by the mentor character), comparing player’s decisions with recommendations from clinical guidelines [1,29-31]. Correct decisions lead to gaining points and progression in the game. At every step, the game offers additional learning resources: help files (eg, algorithms, summaries, and clinical pearls), orientation from the mentor, and links to bibliographic references.

### Usability and Playability Evaluation

The next step will be the usability and playability assessments. For this, we will enroll 4 physicians who work in Londrina, Brazil (2 female and 2 male; 2 with gaming/computer previous experience and 2 without experience) and 4 undergraduate medical students from Universidade Estadual de Londrina (UEL) (2 female and 2 male, with and without gaming experience), who will play the game on a desktop computer, in a controlled environment, each participant alone in a single session. Usability data will be assessed using Web-based System Usability Scale (SUS), as previously described by Brooke [32], and playability will be assessed by Web-based Heuristic Evaluation for Playability, as described by Desurvire et al [33] The actions of the players will be recorded by the software for further analysis by the researchers ([name], [name]). Further adjustments will be made in the game, according to responses obtained in this phase of the study.

### Educational Efficacy Assessment

After final adjustments in the game, guided by usability and playability assessments, the efficacy of InsuOnline as an educational tool will be assessed in an unblinded randomized controlled trial [34]. We will send a letter of invitation to all primary care physicians (PCPs) who work in Londrina to participate in the study. If those PCPs do not fulfill our sample size, we will also invite PCPs from other cities in the state of Paraná (Brazil), such as Maringá, Curitiba, or São José dos Pinhais. The PCPs who are willing to participate in the study will be included and randomized at study entry, using a random number generator, to 1 of 2 groups. We will exclude clinical endocrinologists or diabetologists.

Physicians enrolled in the Group A will be exposed to InsuOnline. They will be asked to play the game until its end, on the Web (with an individual login) in their own time and rhythm. Physicians enrolled in the Group B will undertake a traditional instructional session, during one afternoon, composed of a short lecture and a group discussion of clinical cases, which will be identical to the ones included in InsuOnline. This traditional instructional session will focus on the same teaching topics of the game, and it will be coordinated by a clinical endocrinologist not linked to the research team in order to avoid potential biases. This endocrinologist will be trained by the researcher endocrinologists, and he will use didactic material prepared by our team.

We will evaluate subjects´ knowledge on insulin therapy using a Web-based questionnaire, containing 10-20 multiple choice questions. The questions will be clinical vignettes of diabetic patients who require initiation and/or adjustment of insulin. For each question, the participant should choose the best option for achieving a better glycemic control, according to current guidelines [1,29-31. Questions regarding insulin therapy will be selected from the American Diabetes Association Self-Assessment Program, Module 2 (Pharmacological Treatment of Hyperglycemia) [35], translated to Portuguese, and adapted to be compatible with the game´s clinical scenarios and learning objectives. Participants´ attitudes regarding diabetes will also be assessed, by the application of Web-based Diabetes Attitudes Scale, version 3 (DAS-3) [36]. The questionnaire and the DAS-3 will be answered by the participants at 3 time points: before the intervention (pre-test), immediately after the intervention (after-test), and 6 months after the intervention (late-test). The average number of right answers will be presented and compared in the different time points within each group (intragroup) using analysis of variance (ANOVA), and between the 2 groups at each time point (intergroup) using Student´s *t* test. A bicaudal significance level of 0.05 will be adopted. Data analysis will be done by intention-to-treat, with last observation carried forward, which means that all randomized participants´ data will be included in the final analysis.

The participants will be asked a few Likert-scale and free text questions at the end of each intervention to assess their general impressions about the intervention (mostly to assess if it was pleasant or enjoyable). Software-recorded data on player´s usage of the game will be analyzed to assess the number of logins, time spent on the game, etc. For the participants in Group A that do not finish the game, the reasons for early withdrawal will be collected by an online questionnaire. We will contact (by phone or email) the participants who do not eventually fulfill the questionnaires at least twice.

In order to detect a minimum standard deviation of 0.5 on the average of right answers with 80% of statistical power at 5% of significance level, we will need to include 128 subjects in our study (64 in each group). We will enroll 160 subjects (80 in each group), in order to compensate for an expected 25% dropout rate.

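### Both post-intervention tests are dated from the end of the intervention, which has no limit in the game arm and no definition for physicians who do not finish

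*Protocol article*

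**What the plan says.** All of the relevant text is in the protocol article, Methods, Educational Efficacy Assessment.

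- **Randomisation.** Willing physicians "will be included and randomized at study entry, using a random number generator, to 1 of 2 groups".
- **Group A.** "They will be asked to play the game until its end, on the Web (with an individual login) in their own time and rhythm". No closing date or access period is given. Under Level Design the game has 16 patients, one per level, and a wrong choice sends the player back to the same level, so the end point depends on each player's pace and success.
- **Group B.** "Physicians enrolled in the Group B will undertake a traditional instructional session, during one afternoon".
- **Tests.** The knowledge questionnaire and the attitude scale are given "before the intervention (pre-test), immediately after the intervention (after-test), and 6 months after the intervention (late-test"). The last two are counted from the intervention, not from randomisation.
- **Non-finishers.** "For the participants in Group A that do not finish the game, the reasons for early withdrawal will be collected by an online questionnaire".
- **Missing questionnaires, either arm.** "We will contact (by phone or email) the participants who do not eventually fulfill the questionnaires at least twice".
- **Analysis.** "Data analysis will be done by intention-to-treat, with last observation carried forward", with a Student t test between groups at each time point.

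**The concern.** The anchor for both outcome tests is a fixed event in one arm and a personal, possibly unreached event in the other. The authors expect some Group A physicians not to finish. For those physicians neither the moment just after the intervention nor the date six months later has a defined start.

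If no after-test is taken, carry-forward supplies the last available score. For a physician with only a pre-test, that means a score of no learning, even after many levels played. Such gaps arise through non-completion of a long self-paced task in Group A, and only through missing a single afternoon or not answering in Group B. Unequal missingness is therefore a natural result of the design. All randomised physicians would be in the analysis, but for non-finishers the value could be an imputed one that depends on adherence in one arm. An after-test not taken at the time cannot be recovered later.

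**Working it through.** **1. The passages side by side**

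| Item | Group A | Group B |
|---|---|---|
| Length of intervention | until the game ends, self-paced | one afternoon |
| After-test due | when the physician finishes | after the session |
| After-test due if not completed | not defined | not defined, but the session has a date |
| Late-test due | 6 months after finishing | 6 months after the session |
| Rule if no score | carry forward | carry forward |

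The reminders do not close the gap. A questionnaire is outstanding only once it is due, and no due date exists for a non-finisher. Carry-forward has the same difficulty, because it needs a rule for when the after-test counts as missing.

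**2. Scale**

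The plan gives no figure for this effect. Its sample size sets the scale: a difference of 0.5 SD, 80% power and two-sided 5% give 63.77 per arm by the t distribution. That rounds up to 64 per arm and 128 in total, as stated. Enrolment is 80 per arm, and since all randomised physicians are analysed, n = 80 per arm is used below.

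**3. Bias from carry-forward**

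Assumptions, none of them in the documents (which give only an overall 25% dropout):

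- Within-arm SD is 1.
- The true gain g is the same in both arms and is shared by physicians who are not tested.
- Fractions pA and pB lack an after-test and carry the pre-test forward.

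Formulas:

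- Expected difference, A minus B = g(1 − pA) − g(1 − pB) = −g(pA − pB). The true difference is 0, so this is all bias.
- Pooled SD = √{1 + g²[pA(1 − pA) + pB(1 − pB)]/2}.
- Rejection rate: two-sided 5% t test, 80 per arm, at the standardised difference.

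Worked case, g = 1, pA = 0.35, pB = 0.15: the difference is −0.20. The SD is √{1 + (0.2275 + 0.1275)/2} = √1.1775 = 1.085. The standardised difference is −0.184 and the rejection rate is 21.2%.

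| g (SD) | pA | pB | Bias (SD) | Rejection rate |
|---|---|---|---|---|
| 1 | 0.35 | 0.15 | −0.20 | 21.2% |
| 0.5 | 0.35 | 0.15 | −0.10 | 9.4% |
| 1 | 0.25 | 0.15 | −0.10 | 9.0% |
| 0.5 | 0.25 | 0.15 | −0.05 | 6.1% |
| 1 or 0.5 | 0.25 | 0.25 | 0 | 5% |

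**4. What the untested physicians learned**

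Let untested physicians gain hA and hB. Measured against the true as-randomised difference, the bias is −(pA·hA − pB·hB). With pA = 0.35 and pB = 0.15:

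- hA = hB = 1 gives −(0.35 − 0.15) = −0.20.
- hA = hB = 0.5 gives −(0.175 − 0.075) = −0.10.
- hA = hB = 0 gives 0. The carried-forward scores are then right, and the observed 0.20 SD deficit (at g = 1) is a real result of lower completion.
- hA = 0.5 and hB = 0 (partial play, no attendance) gives −0.175.

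For a common untested gain between 0 and 1 SD, the bias therefore runs from nil to 0.20 SD.

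**The case against.** **The tests are not restricted to finishers.** A reader might infer that non-finishers get no after-test at all, or are asked only for their reasons. The text does not support that. The tests are set for participants generally, and anyone in either arm who does not return a questionnaire is contacted at least twice. Investigators may in practice test non-finishers. This objection stands: the fault is the lack of a defined due date, and carry-forward of the pre-test is the probable consequence, not a stated rule.

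**The size is assumed.** The 35% and 15% are not in the documents, and the 0.20 SD is wholly bias only if untested physicians gained the full 1 SD. A Group B physician who missed the session may truly have gained nothing, and a Group A physician who stopped early may have gained part. This also stands. The 21% is a scenario and not the type I error of this trial.

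**Self-pacing is deliberate, and testing each arm straight after its teaching is reasonable.** This stands too. Six months from a person's own exposure is a defensible anchor for a retention outcome, so a single calendar date for all late-tests is not required. A reader might also infer that variable time since randomisation is confined to Group A. The interval from randomisation to the Group B session is not stated either, so this is not shown.

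**An article condenses.** Access windows and logistics may sit in a fuller protocol. For the same reason, the absence of a reasons questionnaire for Group B physicians who miss the session is no finding. But the article itself fixes the anchor, the open-ended duration, the label for non-finishers and carry-forward. It is their combination that makes measurement depend on completion, and that is more than an omitted detail.

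**Conclusion.** The concern holds in this form: the end of the intervention is unbounded in Group A and undefined for its non-finishers, so their after-test and late-test have no due date. Followed as written, the plan would probably replace their outcomes with earlier scores, in one arm more than the other.

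The documents do not fix the size or even establish that bias will occur. It needs unequal missingness, or unequal gains among the untested, together with untested physicians who did learn something. In the scenarios shown with a common gain, the bias runs from nil to 0.20 SD against the game. The upper figure would be two fifths of the 0.5 SD difference the trial is sized to detect (0.20/0.5 = 0.4). This is a cheap improvement worth making before enrolment. It is not evidence that the trial cannot answer its question.

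**What to change.** 1. State a maximum play window counted from randomisation. Its length is for the investigators to choose.
2. Send the after-test to each Group A physician on finishing or, if not finished, at the end of the window. Send it to each Group B physician after the session or, if not attended, at the end of the same window.
3. Send the late-test 6 months after that person's after-test due date, so that everyone has a due date and the interval is kept at the individual level.
4. Tie the planned reminders to these due dates, and analyse all physicians as randomised using the observed scores.

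**Cost.** A few lines of protocol text and an automatic email from the Web questionnaire already planned. Play time becomes bounded, and some physicians are tested before finishing. After-test timing will still differ somewhat between arms, because self-pacing is kept. Any real effect of lower completion will remain in the result, as it should in an as-randomised comparison.

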Also, this is the first known research trial studying the educational efficacy of a computer game in teaching PCPs about insulin therapy for DM. This is important, as most games for health care have not been validated as tools for education or health outcomes improvement, and there is a great need of good quality studies which can provide good scientific evidences to support the fast-growing field of games for health. Therefore, our study was designed to follow the rigorous guidelines for research on games´ effectiveness proposed by Kato [44].

We hope to demonstrate that a game can be an attractive and effective option for CME on insulin and diabetes. If we can do that, it would give more support to the idea that games can be very good options for large-scale CME, since they can be published on the Web to reach more health professionals compared to traditional learning activities, such as conferences or symposia, which cost substantial amount of time and money. A well-designed Web-based learning game can be used by the learners in their own time and rhythm, at possibly smaller costs, and have a number of significant potential advantages.

In conclusion, we demonstrated that the design and development of a game for education of PCPs on insulin management is possible with the collaboration of a multidisciplinary team. Although its efficacy still needs further evaluation, we think that InsuOnline can be a valuable tool for large-scale CME on DM, in view of its easy dissemination on the Web, customizable content, and accordance with adult learning principles. We hope it can contribute to improving PCPs´ knowledge and optimize DM control in primary care.

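### Within-group ANOVAs over time stand beside the between-group t test with no statement of which decides efficacy, and the between-group test ignores the pre-test score

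*Protocol article*

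**What the plan says.** All the relevant text is in the protocol article, mostly under Educational Efficacy Assessment. The efficacy of the game "will be assessed in an unblinded randomized controlled trial" with two arms: the game, or a traditional teaching session. On timing, "The questionnaire and the DAS-3 will be answered by the participants at 3 time points". The article lists these occasions as "before the intervention (pre-test), immediately after the intervention (after-test), and 6 months after the intervention (late-test").

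One sentence fixes the analysis of the mean number of right answers. The scores are to be "compared in the different time points within each group (intragroup) using analysis of variance (ANOVA"), and also "between the 2 groups at each time point (intergroup) using Student´s *t* test". On the error level, "A bicaudal significance level of 0.05 will be adopted". The form of ANOVA is not given, neither comparison is named as the one that decides efficacy, and the pre-test score has no stated role in comparing the arms at the later tests.

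The sample size of 64 per group is set "In order to detect a minimum standard deviation of 0.5 on the average of right answers with 80% of statistical power" at the 5% level. The Discussion gives the aim: "We hope to demonstrate that a game can be an attractive and effective option for CME on insulin and diabetes".

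**The concern.** The same physicians answer the questionnaire three times. Familiarity with the questions, and any study outside the trial, can raise scores in both arms. A significant rise within the game arm therefore shows that scores went up, not that the game raised them. Randomisation protects only a comparison between arms.

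The plan gives the within-group tests and the between-group test equal standing. If the between-group result is null, a significant before-after rise in the game arm is still available under the stated plan to support the claim that the game is effective.

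The between-group side has a second, smaller weakness. Every participant supplies a pre-test score, yet the arms are compared on unadjusted means at each time point. One of those time points is the pre-test, where randomisation already makes the null hypothesis true and the test answers no useful question.

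**Working it through.** **Inputs from the protocol article:** two-sided 5% level, 80% power, 64 per group, three tests per participant. The stated effect of 0.5 is read as a standardised difference of 0.5 SD. **Assumed, because the article gives neither:** correlation ρ between any two tests of 0.3, 0.5 or 0.7, and a retest gain of 0.5 SD at both later tests, identical in both arms. Scores are taken as normal with equal variance and equal correlations.

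**1. The plan's own figure.** For a two-sample t test with d = 0.5, the normal approximation is n = 2(1.960 + 0.842)²/0.5² = 62.8, so 63 per group. The t-based calculation gives 63.8, so 64 per group, with power 0.801 at 64. The stated size reproduces, and it belongs to the between-group t test.

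**2. What the within-group test does under a shared retest gain.** Here the game adds nothing over the comparator: both arms shift by (0, 0.5, 0.5) SD. In one arm of n = 64, the repeated-measures F test has 2 and 126 degrees of freedom. Its noncentrality is λ = n × Σ(shift − mean shift)² / (1 − ρ). The sum is (1/3)² + (1/6)² + (1/6)² = 1/6, so λ = 10.67/(1 − ρ).

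| ρ | λ | Within-group test significant (20,000 simulated trials) |
|---|---|---|
| 0.3 | 15.2 | 94% |
| 0.5 | 21.3 | 99% |
| 0.7 | 35.6 | over 99% |

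In the same setting the between-group t test at a later time point rejected in 4.9% of simulated trials, which is its nominal level. The shared gain cancels between arms but not within an arm.

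**3. What ignoring the pre-test costs.** Adjusting for pre-test multiplies the residual SD by √(1 − ρ²), so the effective standardised difference is 0.5/√(1 − ρ²). An unadjusted difference in change has SD √(2(1 − ρ)), so its effective difference is 0.5/√(2(1 − ρ)). Power at 64 per arm, two-sided 5%:

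| ρ | Planned t test | Adjusted for pre-test | Unadjusted change score |
|---|---|---|---|
| 0.3 | 80% | 84% (effective d 0.524) | 66% (effective d 0.423) |
| 0.5 | 80% | 90% (effective d 0.577) | 80% (effective d 0.500) |
| 0.7 | 80% | 98% (effective d 0.700) | 95% (effective d 0.645) |

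Baseline adjustment beats the planned test at each of these correlations. A plain comparison of change scores does worse than the planned t test when ρ is below 0.5, so the adjustment matters and not merely the use of the pre-test.

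**4. If the ANOVA were one-way.** Treating the three scores as independent would give a true type I error of 1.4%, 0.3% and 0.01% at ρ = 0.3, 0.5 and 0.7. Power for a 0.3 SD shift at both later tests would be 34%, 29% and 23%, against 53%, 69% and 90% with the repeated-measures error term. The fault would be lost power, not false positives.

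**The case against.** The strongest reply is that the randomised comparison is already planned, in the same sentence as the ANOVA. The sample size is built on it, a retest effect common to both arms cancels in it, and under randomisation the arm difference at a later test has the same expectation as the arm difference in change. All of that stands. Omitting the pre-test costs precision, not validity. It does not settle which of the two tests supports the efficacy claim.

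Three stronger readings are tempting, and the article does not support them:

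- **That the plan treats paired scores as independent.** The article says only ANOVA, which includes repeated-measures ANOVA, and a condensed article may leave the error term to a fuller document. The one-way results in step 4 are conditional on a reading that the text does not establish.
- **That no randomised evidence of efficacy is planned.** The t test provides it. What is absent from the stated analysis is use of the pre-test score in that comparison.
- **That the investigators will read significance in one arm but not the other as a difference between arms.** Nothing in the article proposes this, and the Discussion sentence states a hope, not a decision rule. One could calculate that, with an identical 0.25 SD gain in both arms and ρ = 0.5, exactly one arm is significant on a paired test in 50% of trials. But the formula 2q(1 − q), with q the power in one arm, cannot exceed 50%, and that gain puts q near one half. At ρ = 0.5 the figure is 22% for a 0.1 SD gain and 5% for 0.5 SD. It should not be quoted as the size of this problem.

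**Conclusion.** The point holds as one of ranking and precision. The article sets formal within-group tests beside a valid between-group test and does not say which decides efficacy. The within-group test is no evidence for the game: with a shared 0.5 SD retest gain it would be significant in about 94% to over 99% of trials, against about 5% for the between-group t test. Leaving out the pre-test forgoes roughly 4, 10 or 18 percentage points of power at ρ = 0.3, 0.5 or 0.7.

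These sizes rest on the assumed correlations, the assumed retest gain and 64 analysed per arm. The plan enrols 80 per group and carries the last observation forward, so the analysed number could be larger. That would change the percentages but not the conclusion. A smaller retest gain would make the within-group test significant less often: at 0.2 SD the figures are 27%, 35% and 54% for ρ = 0.3, 0.5 and 0.7, still well above 5%.

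**What to change.** - State that the efficacy conclusion rests on the between-arm difference in right answers at the after-test and the late-test, adjusted for pre-test score and reported with 95% CIs. ANCOVA at each time point would do. So would one repeated-measures model with visit and arm-by-visit terms, with the pre-test either as a covariate or as an outcome whose baseline means are constrained equal across arms.
- Do not substitute an unadjusted difference in change, which can have less power than the planned t test.
- Drop the between-group test at pre-test.
- Report within-arm change as means with CIs, labelled descriptive. If any within-arm test is kept, name it as repeated-measures so that its error term respects the pairing.

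The cost is a change of wording in the analysis plan. The pre-test is already collected, so no extra data, visits or participants are needed, and the stated 64 per group remains sufficient.
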